### Sample size

There are few published studies reporting HbA1c change following lifestyle or pharmaceutical intervention in pre-diabetes. For example, a trial in those with pre-diabetes by Defronzo et al. [53] on a drug intervention using pioglitazone reported a point estimate of the reduction in HbA1c of 0.24% (2.6 mmol/mol) relative to placebo. In T2DM a clinically important difference with drug interventions is 5 mmol/mol. Past research reports an SD for HbA1c in similar clinical samples to those with pre-diabetes of between 4 and 6 mmol/mol [54]. Based on the larger of these SDs, a sample size of 32 in each main effects arm has 90% power to detect a 5 mmol/mol reduction with a type I error rate of 5%. Accounting for 25% drop-out, a total sample size of 88 is needed (22 in each factorial combination). The power to detect differences is likely to be improved using baseline HbA1c as a continuous covariate. However, an uncertainty for this study is whether the minimal clinically important difference for reduction of HbA1c in the setting of pre-diabetes should be anticipated to be closer to that seen in the pioglitazone study (increasing the required sample size), and that the SD for the HbA1c is likely to be smaller in pre-diabetes than in T2DM (decreasing the required sample size). For 80% power to detect a difference of 2.6 mmol/mol with an SD of 4 and 25% drop-out, a total recruitment of 92 is needed, and for 90% power *n* = 136. For a difference of 3.8 mmol/mol, half-way between the two values, and the larger SD of 6, a total sample size of 152 participants with 38 in each factorial combination will be recruited for this study.

### Analysis plan

All primary analyses will be based on intention-to-treat principles with all individuals analysed in the group to which they were randomized. Demographic and baseline characteristics will be summarised using descriptive statistics. The primary outcome is HbA1c at 6 months. The primary analysis for the main outcome variable will be analysis of covariance (ANCOVA) with the baseline measurement of HbA1c as a continuous covariate, and the randomized treatments as main effects, and their interaction as categorical explanatory variables. Adjusted analyses will be conducted to include potential baseline confounding variables (BMI, level of exercise and total daily energy intake), and whether medications that could affect glucose metabolism were used after randomization. The effect of change in weight, change in exercise, and change in total daily energy intake between baseline and 6 months on HbA1c will also be explored using ANCOVA. A linear mixed model using all of the three HbA1c measurements and an appropriate random effects structure to account for correlation between repeated measurements, and using HbA1c at baseline as a continuous covariate, will be used as a sensitivity analysis for the effect of the randomized treatments. Subgroup analysis will use interaction terms (with treatment) for whether treatment effects vary by ethnicity, sex, or socioeconomic status.

Secondary outcome variables will be analysed in a similar way, with the most important outcomes for each being the 6-month time point. All outcome variables will be analysed with their baseline value as a continuous covariate. Subsequent sensitivity analyses will be guided by the outcome of this, with the introduction of relevant baseline covariates for each outcome variable. Factors which may affect mental health and well-being outcomes such as alcohol, recreational drug use, and life stressors will be described and considered in the analysis. Additional file 3 contains tables for baseline characteristics and results.

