### Prebiotics and fibre

Prebiotics are nondigestible high-fibre food components that are selectively fermented by particular members of the gut microbiota providing benefits to the health of the host [22]. Both soluble and insoluble fibre intake are important for prevention and treatment of T2DM, obesity, CVD, and hyperlipidaemia [23, 24].

Specifically, β-glucans are soluble polysaccharide prebiotics with a high molecular weight and are present in a range of noncereal and cereal foods, including oats and barley [25, 26]. The health properties of β-glucans are well documented [23, 26–31]. A 2018 meta-analysis of oat β-glucan (median dose 3.5 g/day) including data from 58 trials (*n* = 3974) found modest reductions in low-density lipoprotein (LDL; 0.19 mmol/l), non-high-density lipoprotein cholesterol (non HDL-C; 20 mmol/l), and apolipoprotein B (0.03 g/l) [32]. The European Food Safety Authority (EFSA) has endorsed claims that 4 g β-glucan significantly reduces blood glucose after meals, and 3 g/day decreases blood cholesterol [33]. However, to our knowledge there is little published evidence of the long-term effects of β-glucan and in particular whether these effects result in achievement and long-term maintenance of normal blood glucose concentrations, which is fundamental in decreasing the risk of developing T2DM.

Based on the above evidence of benefits from oat-derived β-glucan, in this research we will pair β-glucan with HN001. Furthermore, in vitro research indicates that β-glucan supports the growth of HN001 [34]. We contend that, in contrast to a probiotic-only intervention, this modification will most benefit metabolic and mental health outcomes.

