## Methods/design

### Randomized controlled trial design and hypotheses

This is a 2 × 2 factorial design, randomised, parallel-group, placebo-controlled trial in 152 adults with pre-diabetes designed to test the hypotheses that the administration of 6 months of the probiotic HN001 (6 × 10^9^ cfu) either alone or in combination with a cereal enriched with 4 g β-glucan to adults with pre-diabetes for 6 months will reduce glycated haemoglobin (HbA1c). The allocation ratio to groups will be 1:1:1:1. The design is to test the superiority of HN001 with or without 4 g β-glucan over placebo.

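### The hypotheses, the sample size and the primary model do not agree on which contrast decides the trial; the factorial margin has about 92% power, a single-factor cell contrast about 65% before any gain from baseline adjustment

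*Protocol article*

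**What the plan says.** Three sections of the protocol article bear on the primary test.

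- **Randomized controlled trial design and hypotheses.** The hypothesis is that HN001, by itself or together with the β-glucan cereal, lowers HbA1c. The section adds: "The design is to test the superiority of HN001 with or without" the β-glucan cereal, with placebo as comparator. It gives no hypothesis for β-glucan on its own. Allocation is equal across the four cells.
- **Sample size.** The calculation works on factorial margins: "a sample size of 32 in each main effects arm has 90% power to detect a 5 mmol/mol reduction". It inflates for loss: "Accounting for 25% drop-out, a total sample size of 88 is needed (22 in each factorial combination"). The adopted 152 (38 per cell) is tied to 3.8 mmol/mol and SD 6, but no power is attached to it.
- **Analysis plan.** The primary ANCOVA has baseline HbA1c as covariate "and the randomized treatments as main effects, and their interaction as categorical explanatory variables". It does not say which contrast decides the trial or how the factors are coded.

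The Prebiotics and fibre section gives a reason to expect that the two agents may not act independently: "in vitro research indicates that β-glucan supports the growth of HN001".

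**The concern.** In a 2 × 2 factorial trial, the effect of HN001 can mean two things. One is the margin: all HN001 participants against all placebo-capsule participants, averaged over cereal. The other is a simple effect or cell contrast, such as HN001 with control cereal against double control. The margin uses all participants and the cell contrast uses half of them.

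The sizing fits the margin. The hypotheses can be read as cell contrasts. The model can deliver either, depending on coding. Under reference coding, the HN001 coefficient in a model with the interaction is the simple effect at the reference cereal. Under effect coding, it tests the equally weighted margin. Two competent analysts could therefore report different primary results from the same data and the same stated model.

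The two readings also answer different questions. The combination cell against double control changes both capsule and cereal, so β-glucan alone could produce a positive result that is then credited to HN001.

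**Working it through.** **Inputs, all from the Sample size section unless marked**

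- Type I error 5%. Sidedness is not stated; two-sided is assumed because it reproduces the article's 32 per arm, where a one-sided test would need about 26.
- Adopted design: difference 3.8 mmol/mol, SD 6, 25% drop-out, 152 recruited.
- Completers: 152 × 0.75 = 114, so 57 per margin side and 28.5 per cell.
- Baseline correlation: not given, so shown as a range (assumption).

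**Step 1: reproduce the article's own figure.** For 5 mmol/mol, SD 6, 90% power and two-sided 5%, a two-sample t calculation gives 32 per arm (90.7% power; 31 gives 89.8%). Two arms of 32 make four cells of 16. Then 16 ÷ 0.75 = 21.3, rounded up to 22, and 22 × 4 = 88. Both stated figures reproduce, and they do so on margins.

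**Step 2: standard errors at the adopted size, without covariate gain**

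- Margin: 6 × √(2 ÷ 57) = 1.12
- Cell contrast: 6 × √(2 ÷ 28.5) = 1.59
- Interaction (difference of two simple effects): 6 × √(4 ÷ 28.5) = 2.25

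**Step 3: power at 3.8 mmol/mol (noncentral t), with the ratio of 3.8 to the standard error**

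- Margin, 57 v 57: ratio 3.38, power 91.8%
- Single-factor cell contrast, 28.5 v 28.5: ratio 2.39, power 65.1%, or 65.9% with the error pooled over four cells
- Interaction of 3.8: ratio 1.69, power 39%

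**Step 4: effect of keeping the interaction in the model.** In balanced cells the equally weighted marginal contrast keeps SE 1.12, and power stays at 91.8%. Under reference coding the HN001 coefficient has SE 1.59, which is the cell-contrast line above. The loss comes from which contrast is read, not from the term.

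**Step 5: gain from the baseline covariate.** The residual SD becomes 6 × √(1 − r²). For the cell contrast with pooled error, at assumed values of r:

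- r of 0: residual SD 6.00, cell power 66%, margin power 92%
- r of 0.3: residual SD 5.72, cell power 70%, margin power 94%
- r of 0.5: residual SD 5.20, cell power 78%, margin power 97%
- r of 0.7: residual SD 4.28, cell power 91%, margin power 99.7%

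With SD 4, the lower end of the article's range, and no covariate gain, cell power is 94%.

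**Step 6: size needed for cell contrasts at SD 6, no covariate gain.** For 80% power, 41 completers per cell: 41 ÷ 0.75 = 54.7, rounded up to 55, and four cells of 55 make 220 recruited. For 90%, 54 per cell: 54 ÷ 0.75 = 72, and four cells of 72 make 288. The plan recruits 152.

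**Step 7: two alternative effect patterns**

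- HN001 works only with β-glucan: the margin is the mean of 3.8 and zero, which is 1.9, and marginal power is 39%.
- Both agents act additively at 3.8 each: the combination against double control is 7.6, and power exceeds 99%.

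**The case against.** The strongest reply is that the article is consistent if read as a plain factorial trial. The superiority sentence fits HN001 across both cereals. The sample size speaks of main-effects arms, the model lists the treatments as main effects, and the Discussion describes HN001 against placebo within a factorial design with an active and a control cereal. Coding is normally settled in an analysis plan, which is not shown.

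Much of this stands. A reader might infer that the hypotheses simply are cell contrasts. The documents do not support that: the wording about use alone or in combination leans that way, but the superiority sentence and the Discussion also fit the margin. A reader might also infer that the interaction term halves the effective sample. It does so only if reference-coded coefficients are taken as the treatment effects, and the article does not specify that coding. Finally, 65% should not be read as the power of every stated hypothesis. It ignores the covariate gain that the article expects, uses the upper SD, and does not apply to the combination against double control if the effects add.

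What the reply does not remove is that the article itself states hypotheses, sizing and primary model, and no sentence ties the three to one contrast. Coding may be left to an analysis plan. Which effect is primary should not be, when the hypotheses and the sizing point in different directions.

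**Conclusion.** The point holds as a mismatch. The deciding primary contrast is not named, and the three sections do not point to the same one. At 3.8 mmol/mol, SD 6, 25% drop-out and two-sided 5% (assumed), without covariate gain, the margin has about 92% power and a single-factor cell contrast about 65%. The 92% is back-calculated, since the article attaches no power to 152. With baseline correlations of 0.3 to 0.7 (assumed), cell power is about 70% to 91%. An interaction of 3.8 has about 39% power without covariate gain. The shortfall bears chiefly on HN001 alone against double control. The sample size itself is adequate for the margin, and the interaction term may stay in the model.

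**What to change.** In the Analysis plan, state that the primary contrast is HN001 against placebo capsule, averaged over cereals. State whether β-glucan against control cereal, averaged over capsules, is a second primary or a secondary contrast; if both are primary, say how multiplicity is handled. Estimate the margins either from the model without the interaction or, with it, as equally weighted (effect-coded) marginal means. Either route serves.

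Report the interaction with its confidence interval and the four cell means as secondary. Reword the hypotheses section to match, including the status of β-glucan. Add to the Sample size section that cell contrasts and the interaction are not what 152 was sized for.

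The cost is wording only; recruitment, randomisation and data collection do not change. The drawback is that, if the interaction is real, the marginal effect averages over it: under the pattern in which HN001 works only with β-glucan, the margin shrinks to 1.9 mmol/mol with 39% power. Reporting the interaction and cell means discloses this but does not restore the power. If the investigators want the cell contrasts to decide the trial, the sample size must be recalculated for them, with a stated baseline correlation.

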#### Concomitant care

To ensure all participants have access to a similar baseline knowledge of pre-diabetes, all participants will be given a standard information pamphlet about pre-diabetes at the enrolment visit. Study participants will be advised to use the study interventions daily (as described above), and apart from this to continue with their current routines. All participants will be given a record of their anthropometric measures at each study visit. Physical activity levels and dietary intake will be measured by the Stanford Leisure-Time Activity Categorical Item questionnaire (L-Cat 2.2) [38] and 3-day diet diary at every study time point. These data will be used in the analysis to control for the effects of changes in activity and diet.

Throughout the study, all participants will continue with their usual healthcare provided by their general practitioner. Any change to care such as commencing medications which may impact on study outcomes will be collected and adjusted for during the analysis.

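### The supportive adjusted analyses, and the loose wording under Concomitant care, adjust for variables measured after randomization; the primary ANCOVA does not

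*Protocol article*

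**What the plan says.** The Analysis plan section of the protocol article sets out several layers of analysis for HbA1c.

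- **Primary model.** ANCOVA of 6-month HbA1c "with the baseline measurement of HbA1c as a continuous covariate, and the randomized treatments as main effects, and their interaction as categorical explanatory variables". The governing principle is intention to treat: "All primary analyses will be based on intention-to-treat principles with all individuals analysed in the group to which they were randomized".
- **Adjusted analyses.** These add baseline BMI, exercise level and energy intake and, in the same sentence, "and whether medications that could affect glucose metabolism were used after randomization".
- **Change scores.** "The effect of change in weight, change in exercise, and change in total daily energy intake between baseline and 6 months on HbA1c" is to be explored by ANCOVA.
- **Mixed-model sensitivity analysis.** The only covariate named is baseline HbA1c.

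The Concomitant care section is broader. Of the activity questionnaire and diet diary completed at every time point it says: "These data will be used in the analysis to control for the effects of changes in activity and diet". Of changes in usual care it says that "commencing medications which may impact on study outcomes will be collected and adjusted for during the analysis". Neither sentence says which analysis is meant.

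**The concern.** A covariate measured before randomization cannot be affected by treatment, so adjusting for it is safe. A covariate measured afterwards can be, and the document gives reasons to expect this here:

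- **Weight.** It is a secondary outcome in its own right (Outcome measures, Table 1).
- **Diet and activity.** Cereal allocation is open (Randomization and blinding), so behaviour and care can differ between the cereal arms.
- **Medication.** People already taking drugs that alter blood sugar are excluded (Setting and participants), so use after randomization is mostly new use. Some of it may be prompted by a high HbA1c.

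An estimate reported beside the primary result and called adjusted is easily taken for the more rigorous of the two. If it is pulled toward zero, a real effect could be discounted. The Economic analysis section takes the 6-month change in HbA1c as its effectiveness input without saying which estimate that is. Secondary outcomes are to be analysed in a similar way to the primary, so the same term could be carried over to them.

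**Working it through.** No figure in the protocol is at stake. The first step compares the texts; the second illustrates what the adjustment can do.

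**Step 1: which model contains what**

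| Place | Variables named | Measured after randomization? |
|---|---|---|
| Primary ANCOVA | baseline HbA1c, two treatments, interaction | No |
| Mixed model | baseline HbA1c | No |
| Adjusted analyses | baseline BMI, exercise, energy intake | No |
| Adjusted analyses | glucose-affecting medication | **Yes** |
| Change-score ANCOVA | change in weight, exercise, intake | **Yes**, but worded as exploration |
| Concomitant care | changes in diet and activity; new medication | **Yes**, analysis not named |

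The problem therefore lies in the medication term of the adjusted analyses and in the two unqualified statements under Concomitant care.

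**Step 2: what adjustment does to the estimate**

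In a linear model,

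adjusted effect = total effect − γ × δ,

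where δ is the between-arm difference in the added covariate (given baseline HbA1c) and γ is that covariate's coefficient in the adjusted model. With δ = 0 nothing is lost. When treatment or the outcome process moves the covariate, the term γδ is taken out of the effect.

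The total effect is set at −3.8 mmol/mol, the difference used in the Sample size section. All other inputs are assumptions and are not in the documents.

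*a. Change score on the causal path.*
- 25% of the effect runs through it: −3.8 − (0.25 × −3.8) = −2.85.
- 50% runs through it: −3.8 − (0.50 × −3.8) = −1.9.

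These results follow directly from the assumed shares. They show the mechanism and are not evidence of size.

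*b. Change score moved by treatment, with no effect on HbA1c, but sharing an unmeasured cause with it.* Assume δ = −1. The unmeasured cause has variance 1 and acts on HbA1c with coefficient 1.5. The change score has independent noise of variance 1. Then γ = 1.5 / (1 + 1) = 0.75, and the adjusted effect is −3.8 − (0.75 × −1) = −3.05. Simulation gave −3.06. The estimate shrinks although nothing is mediated.

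*c. Medication started because HbA1c is high.* Assumptions: baseline HbA1c 44 (SD 2.5); 3-month deviation SD 4, of which 70% carries to month 6; residual SD 3; medication starts in everyone whose 3-month value exceeds 48. Uptake is then about 20% without and 5% with active treatment.

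| Drug's own effect on HbA1c | Unadjusted | Adjusted for medication |
|---|---|---|
| none | −3.81 | −3.09 |
| −2 mmol/mol | −3.51 | −3.09 |

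In the first row δ is about −0.15 and γ about 4.8, so γδ is about −0.72, which is the gap between −3.81 and −3.09. The drug does nothing, yet its indicator carries a large coefficient because it marks people with high HbA1c. In the second row the effect regardless of medication is −3.51 and the effect had no one started medication is −3.8. The adjusted value of −3.09 is neither.

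With 70% uptake above a 3-month threshold of 48 or 50, under a separate set of assumptions and again with an inert drug, the shift was smaller: −3.81 unadjusted against −3.63 or −3.70 adjusted.

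**Scale.** With SD 6 and 25% drop-out, 152 × 0.75 = 114 people remain, or 57 per margin. The standard error of an unadjusted difference is 6 × √(2/57) = 1.12 mmol/mol. The medication shifts above (0.1 to 0.7) are smaller than one standard error.

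**The case against.** A reader might infer that the plan conditions its main treatment effect on post-randomization variables and so breaks the randomized comparison. The document does not support that. The primary ANCOVA and the mixed model name no such covariate, and sensitivity analyses of the secondary outcomes are to bring in baseline covariates.

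A reader might also infer that energy intake must differ between arms because the cereal replaces part of the diet. Both cereals are taken daily as a replacement, and the Study cereals section says they are calorie matched, so replacement alone creates no difference. An indirect route, such as satiety or displaced food, remains possible but is not established. For the blinded capsule the document offers no diet pathway at all.

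Three further objections have weight:

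- The change-score sentence already speaks of exploring, and it concerns the effect of those changes on HbA1c. It needs a label at most.
- The medication term covers any drug that could affect glucose metabolism. Steroids, for example, need not be started because HbA1c is high.
- The numerical illustrations rest on invented shares and uptake rates, and one set of medication assumptions moves the estimate by only 0.1 to 0.2 mmol/mol.

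These objections limit the scope and the size of the point. They do not remove the medication term from the adjusted treatment-effect models, and they do not reconcile the unqualified Concomitant care statements with the Analysis plan.

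**Conclusion.** The point holds for the supportive analyses and for the wording under Concomitant care. The primary result is sound in this respect.

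Treatment estimates from a model containing post-randomization medication use, or changes in diet, activity or weight, are not protected by randomization. In every scenario worked through here the bias ran toward no effect, but that direction depends on γδ having the same sign as the treatment effect. The size cannot be derived from the documents: they give no medication rates and no basis for a mediated share. The range shown for medication (3.1 to 3.7 against 3.8 mmol/mol) depends on the assumed thresholds and uptake. It has not been shown that the adjusted analyses would reverse the reading of the trial. The point deserves correction because the term is stated explicitly and is easy to remove.

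**What to change.** 1. **Analysis plan.** Restrict the adjusted treatment-effect models to baseline BMI, exercise and energy intake, and remove the post-randomization medication term.
2. **Concomitant care.** Replace the two general statements with one that agrees with the Analysis plan: the treatment effect comes from the primary ANCOVA, using every HbA1c value whether or not new medication was started. Diet, activity and medication data are described by arm.
3. **Labelling.** Report any model containing medication use, or change in weight, exercise or intake, as exploratory and not as an adjusted treatment effect. Apply the same rule to secondary outcomes.
4. **Optional.** Add a sensitivity analysis that treats new glucose-affecting medication as an intercurrent event, for example a hypothetical strategy with multiple imputation. This choice can be left to the statistical analysis plan.

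The cost is wording in two sections and the loss of one adjusted model. No new data are needed and the sample size does not change.
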